### Neuropsychological performance in AN

Many authors have reported neuropsychological impairments (e.g. deficits in learning and memory tasks) in AN patients. Candidate intermediate phenotypes for AN are cognitive inflexibility (poor set shifting), weak central coherence and social-emotional processing difficulties (e.g. [48–53]). Neuropsychological impairments may be considered the result of lack of energy availability due to the drastically reduced food intake. In addition, the above mentioned alterations in the HPG as well as the HPA axis may play a role.

Compelling evidence indicates that glucocorticoids are essential for cognitive functions due to influences on brain regions crucial to attention, learning and memory, such as the prefrontal cortex, hippocampus and basolateral amygdala. The hippocampus appears to be particularly sensitive to increased levels of glucocorticoids, possibly because it is dense with glucocorticoid receptors [54, 55]. High cortisol levels in AN patients have been associated with structural brain abnormalities and weak cognitive performance [56, 57], as well as learning and memory impairments [58]. As in animal models, prolonged hypercortisolemia was associated with reduced hippocampal volume measured by magnetic resonance imaging (MRI), which was partially reversed following cortisol decrease during treatment [59]. The duration of illness (and of hypercortisolemia) seems to be a crucial factor, as the degree of hypercortisolemia could not be associated to cognitive dysfunctions in non-chronic AN patients [60, 61]. In general, such changes resolve with weight rehabilitation during inpatient treatment [62], although in some cases, circumscribed persistent deficits are found before and after short-term weight rehabilitation [33, 63].

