### Neuropsychological performance

In addition, the neuropsychological performance of the subjects will be assessed using a neuropsychological battery consisting of the following tests: a) a test for evaluation of verbal intelligence and speech comprehension (“Wortschatztest”, WST; [105]), b) the Trail Making Test (TMT) [106] for the assessment of executive function, attention, information processing speed and planning ability, c) the WCST [107] as a test of frontal brain function. The test examines categorization ability among different categorization options and has an excellent sensitivity with regard to disturbed problem solving and perseverations, d) a go/no-go task as a paradigm for response inhibition, thus refraining an action initiation [108]. This task was programmed with Presentation® software (Version 16.0, Neurobehavioral Systems, Inc., Albany, CA, USA) to assess impairment of inhibitory control in response to food-related and control stimuli (for a detailed description see [109]). Changes on each test will be reported.

The neuropsychological assessment will be repeated after the 10-week intervention period.

A follow-up visit six weeks after EOT is scheduled. A summary of all study procedures is given in Table 1.

**Table 1 Tab1:** A synopsis of study procedures from visit 1 (V1) to visit 7 (V7)

	V1	V2	V3	V4	V5	V6		V7
	Screening	Baseline	Treatment start	Week 2	Week 6	Week 10 (EOT)		End visit (EOS) week 16
	month − 2 ± 2	day − 3 (±2)	day 1	day 15 (±3)	day 43 (±3)	day 73 (±3)		day 113 (±7)
Randomization			X					
Intake of study drug			X------>	-----------	------------	--------X		
Information about study objectives and informed written consent	X							
Inclusion and exclusion criteria	X	X						
Medical history		X						
Sociodemographic data		X						
Anthropometric data (height, weight, waist Circumference, hip circumference, BMI)		X					X	
Weight (BMI)		X	X	X	X		X	X
12-channel ECG		X					X	
Urine pregnancy test		X					X	
Vital parameters (HR, RR)		X	X	X	X		X	
Physical examination		X		X			X	
Gynecological examination		X						
Inclusion criteria and contraindications before first intake (gynecological findings, liver parameters, RR etc.)			X					
EDE-Q			X				X	X
EDI-2			X				X	X
STAI			X				X	X
PHQ-9			X				X	X
EDQOL			X				X	X
Neuropsychological test battery: verbal intelligence test, TMT A and B, Go/NoGo-test with food stimuli, WCST			X				X	
Dexamethasone-suppression test/plasma cortisol concentration (5)			X			X		

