Data of the present study may be used for future sample size calculations of confirmatory studies, as well as for the generation of new hypotheses. The intended statistical analysis follows the intention-to-treat principle. Differences between the treatment groups at baseline will be assessed using Fisher’s test for categorical variables and the non-parametric Mann-Whitney test for metric variables due to the relatively small sample size. For cross-sectional analysis of primary and secondary endpoints, adjustments for potential confounders and group differences at baseline by means of regression models will be applied. Missing outcome values will be imputed by corresponding baseline values. For longitudinal analyses, appropriate mixed models considering the longitudinal structure of data and interrelations due to random patient-specific effects will be used. Due to the robustness of this approach towards missing values, no imputation is planned for the longitudinal analyses. No interim analysis is scheduled. Effect sizes will be reported based on Cohen’s d for group differences for primary and secondary outcomes. Clinical improvements, amelioration in neuropsychological performance and restitution of hormonal aberrancies are all to be considered of clinical significance for patients with AN. The target parameters of safety and tolerability will be analysed descriptively (absolute and relative frequency with confidence intervals, mean values and medians with appropriate distributions).

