### Outcome measures

The primary outcome measure is the change in neuropsychological performance based on the above described neuropsychological test battery after ten weeks of hormonal substitution with an estrogen-progestin-combination. The secondary outcome measures following the 10-week intervention are: a) incidence of treatment-emergent adverse events (AEs) (safety/tolerability) mirrored by the number of AEs (including AEs, adverse reactions [ARs], serious AEs, serious ARs and suspected unexpected serious ARs [SUSARs]), b) changes in psychopathology (EDE-Q, EDI-2, STAI, PHQ-9, EDQOL) mirrored by changes in sum scores, c) changes in cortisol mirrored by changes in plasma cortisol levels during a dexamethasone suppression test as well as changes in plasma concentrations of the appetite-regulating peptides ghrelin, leptin, insulin and glucose during an OGTT and d) changes in antidepressant medication mirrored by changes in their use.

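### Setting missing week-10 outcomes to baseline fixes each missing change at zero, and the article does not say whether this analysis or the mixed model without imputation decides the primary endpoint

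*Protocol article*

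**What the plan says.** The Protocol article, Statistics, commits to intention to treat: "The intended statistical analysis follows the intention-to-treat principle". It then describes regression models for one type of analysis, beginning "For cross-sectional analysis of primary and secondary endpoints, adjustments for potential confounders and group differences at baseline". The next sentence gives the missing-data rule: "Missing outcome values will be imputed by corresponding baseline values". For a second type of analysis, mixed models with patient-specific random effects, the rule is the opposite: "Due to the robustness of this approach towards missing values, no imputation is planned for the longitudinal analyses".

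Under Outcome measures, "The primary outcome measure is the change in neuropsychological performance based on the above described neuropsychological test battery after ten weeks". The battery is given at treatment start (visit V3 in Table 1) and once more: "The neuropsychological assessment will be repeated after the 10-week intervention period". The primary endpoint therefore has two time points, and either description of the analysis could apply to it. The Statistics section does not say which one decides.

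On what happens to cognition without the drug, the background section Neuropsychological performance in AN says: "In general, such changes resolve with weight rehabilitation during inpatient treatment". The same sentence adds that circumscribed deficits persist in some cases.

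**The concern.** When the outcome is a change from baseline, replacing a missing week-10 score by the baseline score asserts that the patient did not change at all. Both arms receive inpatient treatment with monitored meals aimed at weight gain (Data collection, on the EDE-Q), and the background leads one to expect improvement in both. A blanket zero is then a poor guess for many patients.

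Three things are at stake:

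- A real drug effect is diluted by the share of the active arm that is imputed.
- If the arms lose patients at different rates, the arm losing more forfeits more of the improvement common to both. A difference can then appear when the drug does nothing.
- The imputed values are treated as observed. This distorts the SD behind Cohen's d, which the article plans to report. It also affects the variability estimates that the article suggests may serve later sample size calculations.

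Because the same paragraph applies a different rule to its mixed models, one endpoint could also give two answers with no stated order between them.

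**Working it through.** **1. The plan's own figures.** With 25 per arm and a two-sided 5% t-test, the noncentral t distribution gives the following.

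| Effect size | Stated power | Recomputed |
|---|---|---|
| 0.60 | 55% | 54.7% |
| 0.70 | 68% | 67.9% |
| 0.80 | 80% | 79.1% |
| 0.86 | 85% | 84.6% |
| 0.94 | 90% | 90.3% |
| 1.04 | 95% | 95.0% |

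The stated figures reproduce. They describe 25 patients per arm with an outcome.

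**2. Inputs.** From the article: 25 per arm, 1:1 allocation, two-sided 5%, effect 0.80 with SD 1. Not given, so assumed: dropout dT (active) and dC (placebo); improvement common to both arms, μ = 0.5 to 1.0 SD; correlation of baseline with week 10, 0.5 to 0.7; dropout unrelated to outcome. Scores are signed so that higher is better.

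**3. Expected difference after baseline imputation.** With true effect δ, the mean change is (1 − dT)(μ + δ) on active and (1 − dC)μ on placebo. The difference is

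(1 − dT)δ − (dT − dC)μ.

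- 20% missing in both arms, δ = 0.80: 0.80 × 0.80 = 0.64, whatever μ is.
- 30% active, 15% placebo, δ = 0.80: 0.70 × 0.80 − 0.15μ = 0.56 − 0.15μ, which is 0.485 at μ = 0.5 and 0.41 at μ = 1.0.
- 15% active, 30% placebo, δ = 0.80: 0.85 × 0.80 + 0.15μ = 0.68 + 0.15μ, which is 0.755 and 0.83.
- δ = 0 with the same imbalance: ∓0.15μ, which is 0.075 to 0.15 SD against the arm with more dropout.
- δ = 0 with equal dropout: no bias.

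**4. Power and type I error.** Simulation of 20,000 trials per scenario, bivariate normal scores with SD 1, regression of week 10 on arm and baseline. The comparator is the same regression on observed patients only. With two visits and only week 10 missing, this is close to what a likelihood-based mixed model would deliver. Ranges run over correlation 0.5–0.7 and μ = 0.5–1.0.

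| Missing, active / placebo | True effect | Estimate, baseline imputation | Rejection rate, baseline imputation | Rejection rate, observed data |
|---|---|---|---|---|
| 0 / 0 | 0.80 | 0.80 | 89–97% | 89–97% |
| 20% / 20% | 0.80 | 0.64 | 60–82% | 80–93% |
| 30% / 15% | 0.80 | 0.41–0.49 | 28–57% | 78–91% |
| 15% / 30% | 0.80 | 0.76–0.83 | 83–94% | 78–91% |
| 20% / 20% | 0 | 0 | 5% | 5% |
| 30% / 15% | 0 | −0.15 to −0.08 | 6–11% | 5% |
| 15% / 30% | 0 | +0.08 to +0.15 | 6–11% | 5% |

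Part of the fall from 89–97% comes from losing patients and would occur under any method. The share due to the imputation rule is the gap between the last two columns.

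**5. Milder case.** With no common improvement (μ = 0), 20% dropout in both arms and correlation 0.5, power is about 76% with imputation and 80% on observed data. The estimate still shrinks to 0.64.

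**The case against.** A reader might infer that the primary effect will be biased, that power will be lost, and that the background flatly contradicts the rule. The documents do not support that much, for four reasons.

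- **Dropout is not given.** Participants are inpatients with supervised drug intake, and nothing in the article points to losses of 20–30%. With little dropout the rule does little. With more dropout on placebo, power is not lost and the error favours the drug.
- **The background statement is hedged.** It concerns patients undergoing weight restoration and allows for persisting deficits in some. A patient with no week-10 assessment may have left treatment early, and for her little change is possible. The calculations make dropout unrelated to outcome, which favours the remedy. If early leavers really stay near baseline, a missing-at-random analysis would be the optimistic one.
- **A mixed model without imputation is already planned.** Two analyses with different assumptions are not in themselves a contradiction, and ranking them could be left to an analysis plan that is not shown.
- **This is a phase IIa trial** that disclaims confirmatory sizing and aims partly at new hypotheses.

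The first two points stand, so the consequence must be stated as conditional and two-directional. The third limits the work needed but does not remove the point: the baseline rule is stated, not omitted, and it follows directly on the analysis of the primary endpoint. The fourth lowers the severity. It does not excuse the rule, since diluted effects and distorted SDs would pass into the planning of later trials.

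**Conclusion.** The point holds as a should-fix. The article states a rule that sets every missing primary change to zero. This is at odds with, though not strictly contradicted by, its own expectation that cognition generally recovers during inpatient weight restoration. It also leaves open whether this analysis or the mixed model is decisive.

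The size depends on dropout, common improvement and correlation, none of which the article gives. Under the assumptions above, equal dropout of 20% turns 0.80 into 0.64 and costs roughly 10 to 20 points of power beyond what the missing data cost anyway. Unequal dropout can move the estimate either way. When the drug does nothing, it raises the false-positive rate to about 6–11%, provided there is common improvement. With equal dropout and no drug effect there is no bias and the type I error stays at about 5%. It would be wrong to read this as a demonstrated bias in a known direction or as a certain loss of power.

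**What to change.** In the Statistics section, name one primary analysis of the primary endpoint in all randomised patients. The natural choice is the likelihood-based mixed model already planned, with baseline and week 10 as responses, baseline means constrained equal across arms, and the treatment effect taken at week 10. Multiple imputation by arm followed by baseline-adjusted regression would serve equally well. Withdraw baseline-value imputation as the default and keep it as a labelled sensitivity analysis for dropouts who may not have improved, preferably beside one other missing-not-at-random scenario. Apply the same order to the secondary endpoints.

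The cost is a few sentences and no new data. The downside is that the primary result then rests on a missing-at-random assumption, which the sensitivity analysis is there to probe. The change should be dated and made before unblinding.

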### Outcome measures

The primary outcome measure is the change in neuropsychological performance based on the above described neuropsychological test battery after ten weeks of hormonal substitution with an estrogen-progestin-combination. The secondary outcome measures following the 10-week intervention are: a) incidence of treatment-emergent adverse events (AEs) (safety/tolerability) mirrored by the number of AEs (including AEs, adverse reactions [ARs], serious AEs, serious ARs and suspected unexpected serious ARs [SUSARs]), b) changes in psychopathology (EDE-Q, EDI-2, STAI, PHQ-9, EDQOL) mirrored by changes in sum scores, c) changes in cortisol mirrored by changes in plasma cortisol levels during a dexamethasone suppression test as well as changes in plasma concentrations of the appetite-regulating peptides ghrelin, leptin, insulin and glucose during an OGTT and d) changes in antidepressant medication mirrored by changes in their use.

## Discussion

AN is a disorder with high morbidity rates and a severe influence on quality of life. The disorder shows one of the highest mortality rates among all psychiatric-psychosomatic disorders. As a result of restrictive eating patterns and low BMI, neuroendocrinological circuits are regularly altered in AN patients. Indeed, several findings show a compensatory activation of the HPA axis with hypercortisolemia and a suppressed HPG axis with estrogen deficiency. Also with regard to central and peripheral concentrations of appetite-regulating peptides like ghrelin or leptin, AN patients show deviations from the norm. Moreover, it has been shown that clinical symptom amelioration and weight gain are associated with a restitution of dysregulated hormonal circuits.

There are practically no evidence-based pharmacological treatments for AN. The aim of the present trial is to investigate in a randomized, placebo-controlled manner the effects of an estrogen-progestin replacement over ten weeks on the clinical phenotype (disorder-specific and general psychopathology as well as neuropsychological performance) of AN, on the regulation of the HPA and HPG axes and appetite-regulating peptides in AN, but also with regard to safety and tolerability. The only randomized controlled studies available so far have examined the effects of estrogen replacement on bone mineral density in adolescent AN patients. Thus, the trial presented here is the first of its kind.

The results of this clinical trial may have a relevant impact on future treatment regimens in the battle against AN. Novel approaches are necessary to improve rates of AN symptom remission and increase the rapidity of treatment response. Identifying the underlying biological (e.g. neuroendocrinological) factors that maintain AN or may predict patient treatment response represent critical future research directions. Continued efforts to incorporate novel pharmacological aspects into treatments will increase access to evidence-based care and help reduce the burden of AN.
